### Interim analyses {21b}

An interim analysis estimating the SAE rate will be performed when 50% of participants (n=124) are enrolled in the study and reviewed by the data safety monitoring board. The trial will be stopped if the rate of SAEs is significantly greater in the WGS arm as compared to the SOC arm.

### Methods for additional analyses (e.g., subgroup analyses) {20b}

Adjusted analyses will be performed to correct for possible differences in patient characteristics between groups. Subgroup analyses may be performed by drug resistance profile categories.

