### Sample size {14}

The sample size was simulated for the primary objective using a non-linear mixed effect model. We re-calibrated the model described by Svensson and Karlsson [42] using RR-TB patient data from the Free State province to account for differences in study populations. We hypothesize that the intervention will reduce the mean half-life of mycobacterial load (βexp parameter in the model) by 28%. This would correspond to a difference in median time to culture conversion of 4 weeks (12 vs. 16 weeks). Given the equal balance across arms, and a significance level of 0.05, a total sample size of 173 individuals is needed to achieve 90% power to detect the hypothesized effect size. To account for negative or contaminated cultures at baseline (expected 16%) and death or loss to follow-up prior to achieving culture conversion (expected 21%), the total sample size was set at 248 participants.

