## Assignment of interventions: allocation

### Sequence generation {16a}

Randomization 1:1 to the WGS or control arm is automated and performed by Randomizer, a secure dedicated internet site [43].

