### Implementation {16c}

Randomization is web-based [43]. Minimization is implemented to obtain balanced groups by strata of factors associated with time to culture conversion (baseline mycobacterial load as determined by Xpert Ct value or smear microscopy grading), risk of mortality (age, diabetes, HIV status and if HIV positive whether the viral load is suppressed or not) and history of prior treatment with second-line drugs.

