## Statistical methods

### Statistical methods for primary and secondary outcomes {20a}

The primary analysis will be an intent-to-treat analysis. A non-linear mixed-effects model that includes a longitudinal representation of mycobacterial load, probability of bacterial presence in a sputum sample, and a time-to-event model to describe the changes in time to culture positivity in liquid media will be used to compare the bacteriological response between the two trial arms [42]. The feasibility of the WGS strategy will be determined based on the proportion of participants in whom WGS is not successful and the proportion of participants in whom the recommended treatment regimen is not prescribed. For the health economic evaluation, the mean incremental costs incurred by patients and the health care system for the WGS versus the control arm will be estimated. For evaluation of safety, we will compare the SAE rate during treatment between the two arms.

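### Allocation is minimized on prognostic factors, but the article places adjustment only among the additional analyses; if the primary model omits those factors, its test is conservative and its intervals too wide

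*Protocol article*

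**What the plan says.** Three sections of the protocol article bear on this.

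- **Implementation {16c}:** "Minimization is implemented to obtain balanced groups by strata of factors associated with time to culture conversion". The factor given for conversion is baseline mycobacterial load, by Xpert Ct value or smear grade. The other factors are listed for "risk of mortality (age, diabetes, HIV status and if HIV positive whether the viral load is suppressed or not) and history of prior treatment"; that treatment history concerns second-line drugs. Sequence generation {16a} sets the ratio at 1:1.
- **Statistical methods for primary and secondary outcomes {20a}:** "The primary analysis will be an intent-to-treat analysis". The model is described as "A non-linear mixed-effects model that includes a longitudinal representation of mycobacterial load, probability of bacterial presence in a sputum sample", together with a time-to-event part, and it "will be used to compare the bacteriological response between the two trial arms". No covariate is mentioned.
- **Methods for additional analyses {20b}:** "Adjusted analyses will be performed to correct for possible differences in patient characteristics between groups". The covariates are not named, and no link is made to the minimization factors.

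The article does therefore address adjustment. It gives it a secondary place and explains it by possible imbalance.

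**The concern.** Minimization forces the arms to be alike on the chosen factors. Where a factor predicts the response, this removes its contribution to the real variability of the arm difference. A model without the factor still counts that contribution as noise, so the reported standard error is larger than the true one. The test then rejects less often than its nominal level, and the confidence interval is wider than the data justify.

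The reason given in {20b} also fits poorly with {16c}. Factors balanced by design will show little difference to correct. The reason to adjust for them is that the standard error should reflect how patients were allocated. If the plan is carried out as the article reads, the primary result gives up precision that the design has already paid for.

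**Working it through.** **Inputs from the article.** Sample size {14} gives 173 evaluable participants, 90% power, a significance level of 0.05, and an intervention expected to "reduce the mean half-life of mycobacterial load (βexp parameter in the model) by 28" per cent. It allows for losses of 16% and 21% and sets enrolment at 248.

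**Assumptions.** The test is two-sided; the article does not state sidedness. R² is the share of between-patient variance in the response explained by the minimization factors. The article gives no value, so a range is shown.

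**The plan's own figure.** The 173 comes from simulating a re-calibrated model whose variance components are not given, so it cannot be reproduced here. I take 173 and 90% as stated. They imply a standardized effect of 1.960 + 1.2816 = 3.2415 standard errors.

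**Formulas.** Let V be the variance of the arm effect when the factors are ignored. With ideal balance the true variance is V(1−R²). The unadjusted analysis reports V; the adjusted one reports V(1−R²). Hence:

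- true alpha, unadjusted = 2[1 − Φ(1.96/√(1−R²))]
- ratio of interval widths, unadjusted to adjusted = 1/√(1−R²)
- power, unadjusted = Φ((3.2415 − 1.96)/√(1−R²))
- power, adjusted = Φ(3.2415/√(1−R²) − 1.96)

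For R² = 0.20, √(1−R²) = 0.894. Alpha is 2[1 − Φ(2.191)] = 0.028 and the width ratio is 1.118. Power is Φ(1.433) = 92.4% unadjusted against Φ(1.664) = 95.2% adjusted.

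| R² | True alpha, unadjusted | Interval too wide by | Power unadjusted | Power adjusted |
|---|---|---|---|---|
| 0 | 5.0% | 0% | 90.0% | 90.0% |
| 0.05 | 4.4% | 2.6% | 90.6% | 91.4% |
| 0.10 | 3.9% | 5.4% | 91.2% | 92.7% |
| 0.20 | 2.8% | 11.8% | 92.4% | 95.2% |
| 0.30 | 1.9% | 19.5% | 93.7% | 97.2% |

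**Fewer evaluable participants.** If the two losses act in sequence, 248 × 0.84 × 0.79 = 164.6. The standardized effect becomes 3.2415 × √(164.6/173) = 3.162. Unadjusted against adjusted power is then 89.7% vs 91.5%, 91.0% vs 94.2% and 92.5% vs 96.6% for R² of 0.10, 0.20 and 0.30. The gains are 1.8, 3.2 and 4.1 points.

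**Simulation check.** 3,000 minimized trials of 173 were simulated per setting, using a linear model, a biased coin of 0.8 and five factors with assumed frequencies and weights.

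| R² | Alpha, unadjusted / adjusted | Power, unadjusted / adjusted | SE ratio |
|---|---|---|---|
| 0 | 0.053 / 0.051 | 0.898 / 0.899 | 1.00 |
| 0.1 | 0.041 / 0.047 | 0.901 / 0.925 | 1.05 |
| 0.2 | 0.030 / 0.048 | 0.921 / 0.949 | 1.12 |
| 0.3 | 0.023 / 0.054 | 0.927 / 0.969 | 1.19 |

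The Monte Carlo error of an alpha near 5% is about √(0.05 × 0.95/3000) = 0.4 points, so the simulation agrees with the formulas.

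**The case against.** The strongest objection is that the article never calls the primary model unadjusted. Section {20a} is silent on covariates, and a covariate list is commonly left to the full protocol or analysis plan, neither of which is shown. This stands: the unadjusted reading is an inference from {20a} and {20b} together. The point survives because {20b} is not silent. It assigns adjustment a place and a reason, and both fit poorly with minimized allocation.

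Several stronger readings are tempting but not supported.

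- **That adjustment is triggered by the data.** A reader might infer this from the rationale in {20b}. The sentence is unconditional and contains no imbalance test or selection rule.
- **That the factors are strong predictors.** No figure supports this. Only baseline load is tied to culture conversion; age, diabetes and HIV are listed for mortality risk. The baseline sample belongs to the outcome series in Outcomes {12}, and the model has a load component, so baseline load may be partly accounted for already.
- **That the trial is under-powered for this reason.** One might set 88.5%, the power at 164.6 evaluable with R² = 0, against adjusted values of about 92% to 97%. That is not like for like, because balancing also raises the power of the unadjusted test. At the planned 173 the unadjusted power stays at or above 90% throughout the formula table. The drop to about 165 is a separate attrition matter.
- **That adjustment is worth 11%, 25% or 43% more patients.** The ratio 1/(1−R²) describes reported precision. It overstates the gain in power once the arms are balanced.

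Finally, the consequence is conservatism. Neither bias nor excess false positives follows.

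**Conclusion.** The point holds as a moderate one about efficiency and correct interval width. As the article reads, the minimization factors have no stated place in the primary model, and adjustment is justified by imbalance that the allocation method is meant to prevent. If the primary model does omit them and they explain 10% to 30% of the variance, the nominal 5% test runs at about 3.9% to 1.9%, intervals are about 5% to 20% too wide, and about 2 to 4 points of power are forgone relative to adjustment.

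These sizes rest on an assumed R², near-ideal balance, a two-sided test and a linear approximation, which is only a guide to a joint non-linear mixed-effects model. The loss is nil at R² = 0 and may be smaller if the longitudinal component already carries baseline load. If the full protocol or analysis plan already includes the factors in the primary model, what remains is to bring the article's wording into line.

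**What to change.** In {20a}, state that the primary model includes the minimization factors as prespecified covariates: baseline mycobacterial load, age, diabetes, HIV status with viral suppression, and prior second-line treatment. Enter baseline load explicitly, or show that the model's load component captures it. Keep the model without these covariates as a supportive analysis. In {20b}, replace the between-group-differences rationale: the factors are included because allocation was balanced on them and they are expected to be prognostic.

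The cost is wording and a few extra model parameters. The factors must be known at randomization for minimization to run, so no further data collection is needed.

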### Methods in analysis to handle protocol non-adherence and any statistical methods to handle missing data {20c}

The extent of missing data and patterns of missingness will be assessed once all study participants have completed the study. If needed, multiple imputation methods will be used and sensitivity analyses, including complete case analysis, will be conducted to evaluate the impact of missing data on study findings.

### Plans to give access to the full protocol, participant-level data and statistical code {31c}

We will abide by the requirements regarding making the underlying data and statistical code available set by the journal where we publish the results of the main trial outcome results. If not required by the journal, the de-identified dataset generated and analysed as well as the associated statistical codes will be made available after the publication of the main trial outcome results upon request from the corresponding author. Raw sequencing data will be submitted to a public sequence repository (European Nucleotide Archive) as part of the publication process.

## Oversight and monitoring

### Composition of the coordinating centre and trial steering committee {5d}

Several committees monitor the trial. The trial coordinator and field workers of the Clinical Research Organization (Aurum Institute) hold team meetings twice a week to provide day-to-day support for the trial. The central steering committee consists of 5 senior investigators. The central steering committee holds weekly meetings (also attended by the trial coordinator, four laboratory staff and three field workers) to solve any problems that arise during the implementation of the trial. The central clinical committee meets upon request to discuss potential patient safety issues that occur, such as phenotypic-genotypic discordance or failure to achieve culture conversion by week 16 of RR-TB treatment. The central microbiological committee meets upon request to discuss the interpretation of variants identified by WGS in drug resistance candidate genes that are not classified by the WHO catalogue of mutations in *Mycobacterium tuberculosis* [20]. When WGS data indicate possible BDQ resistance, the Free State Provincial Clinical Advisory Committee will be consulted to select the optimal individualized treatment.

### Composition of the data monitoring committee, its role and reporting structure {21a}

The data safety monitoring board (DSMB) consists of three experts in clinical trials and clinical management of drug-resistant TB. The members are independent of the sponsor and the clinical trial team and have no competing interests. The primary role of the committee is to safeguard the interests of the study participants by evaluating the difference in SAE rate between the two arms of the trial. The DSMB will meet when 50% of all participants have been enrolled and whenever required. The DSMB may also be asked to review factors external to the study such as scientific or therapeutic developments that may impact participant safety. Details about the committee are stated in the DSMB charter.

### Adverse event reporting and harms {22}

All SAEs reported to the study staff are reported to Free State University ethics committee and the South African Health Products Regulatory Authority. Because this is a pragmatic trial, all adverse events are managed by the physician in charge of the patient’s care.

### Frequency and plans for auditing trial conduct {23}

All data entered in the electronic database is audited weekly by the team of the principal investigator, independent of the sponsor. The trial conduct is not audited by a team that is independent of the investigators.

### Plans for communicating important protocol amendments to relevant parties (e.g., trial participants, ethical committees) {25}

Important protocol modifications will be communicated to the relevant parties, which may include the central clinical committee, data safety monitoring board, relevant ethics committees, South African Health Products Regulatory Authority, trial registries, and the sponsor.

### Dissemination plans {31a}

The investigators will communicate trial results to the provincial (Free State Province) and national (SA) DoH and the scientific community via presentations at national and international conferences. Results will be published in peer-reviewed scientific journals. De-identified data will be shared at the time of publication as per journal requirements or will be made available upon request.

## Discussion

WGS holds the promise to be a transformative technology in clinical microbiology, especially for slow-growing bacteria such as *Mtb*. While several low TB burden countries have successfully implemented WGS for routine DST, the integration of WGS into routine laboratories in high TB burden countries should be carefully evaluated before the capital investment, operational costs and human resource development required for such endeavour can be justified. Public health policymakers increasingly demand context-specific real-world evidence before implementing a novel intervention. This real-world evidence is most often obtained through observational studies, which are prone to biases. An explanatory RCT could provide an unbiased answer to the question of whether WGS-guided individualized treatment improves time to culture conversion under ideal conditions, not under real-life conditions. We designed a pragmatic RCT to answer the question whether of WGS-guided automated individualized treatment recommendation for RR-TB is effective under routine conditions in high-burden, low-resource settings. The pragmatic trial is designed to provide unbiased real-world evidence by maximizing generalizability while maintaining internal validity.

Several limitations to the trial should be noted. First, while the most important clinical endpoint is 2-year relapse free cure, the lengthy study duration required for this endpoint brings obvious challenges such as high cost and risk of high loss to follow-up rates. We therefore opted to employ a surrogate endpoint and replaced the clinical endpoint with a biomarker. We acknowledge that the surrogate endpoint may not be an accurate indicator for how effective the intervention is. Second, the WHO catalogue of mutations [20] is not exhaustive and knowledge on resistance-causing mutations is incomplete, especially for the new and repurposed drugs. This may reduce the effectiveness of WGS for guiding RR-TB treatments when newer regimens rely mainly on these drugs. Third, because culture-free WGS is still in its infancy, WGS will continue to rely on early positive liquid cultures in the near future. Finally, other molecular technologies are being developed and new treatment regimens are being evaluated. In 2021, the WHO has endorsed the Xpert MTB/XDR, which allows rapid identification of resistance to FQ but does not assess the resistance profile to other drugs included in most of the current and novel RR-TB treatment regimens [19]. The targeted deep-sequencing assay Deeplex Myc-TB can be used directly on sputum specimens with relatively high mycobacterial load for the prediction of resistance to 11 anti-tuberculous drugs/drug classes when investigating 18 of the 50 candidate resistance genes. Using phenotypic DST as the reference, high specificity (≥91%) was achieved for all drugs; sensitivity ranged from 54% for STM to 98% for RIF but could not be estimated for LZD and BDQ [48]. New standardized treatment regimens such as BDQ, Pa, LZD and moxifloxacin (BPaLM) mostly rely on the use of new drugs, making the regimen less prone to amplification of resistance [49]. The role of WGS-directed individualized treatment should thus be evaluated relative to these new developments.

In conclusion, as Cox et al. wrote, “seeking the highest quality of care in all settings should be an ethical imperative for treatment of drug-resistant tuberculosis” [50]. Without individualized treatment guided by drug resistance profiles, routine use of any novel empiric regimen in high RR-TB burden settings will over time result in the emergence of resistance. WGS to determine the complete *Mtb* drug resistance profile has already replaced phenotypic DST in several high-income countries, where precision medicine based on the individual patient and pathogen characteristics is already established. In low- and middle-income countries, WGS is not yet used for clinical care in part due to technical challenges and difficulties in analyzing WGS data and translating WGS information into individualized RR-TB treatment regimens. The use of an individualized treatment recommendation system could overcome this hurdle by automating the individualization of treatment regimen selection and guiding clinicians independent of their level of expertise. Hopefully, quantifying the effectiveness of WGS-guided individualized treatment recommendation for RR-TB treatment, evaluating the feasibility thereof, and assessing health economics from both the health system and patient perspective will play a critical role in answering the question of whether WGS should be recommended for the management of RR-TB in high TB-burden, low-resource settings.

### Trial status

The trial with protocol version 6.0 (June 9, 2021) was registered on the clinical trials.gov register with the number NCT05017324 on August 23, 2021. The first patient was recruited on September 23, 2021, and is expected to be completed by the end of 2022.

## Data Availability

The final de-identified trial dataset will be made available at the time of publication of the main study findings if required by the journal publication policy or via request to the corresponding author if not required by the journal’s publication policy. The investigators are not bound to any contractual agreements that limit such access.

## Abbreviations

AMK: Amikacin
BDQ: Bedaquiline
CCC: Central clinical committee
CFZ: Clofazimine
Ct: Cycle threshold
DLM: Delamanid
DNA: Desoxyribonucleic acid
DoH: Department of Health
DR-TB: Drug-resistant tuberculosis
DSMB: Data safety monitoring board
DST: Drug susceptibility test
EDRWeb: Electronic Drug-Resistant Tuberculosis Register
EMB: Ethambutol
ETO: Ethionamide
FQ: Fluoroquinolone
HIV: Human immunodeficiency virus
INH: Isoniazid
LFX: Levofloxacin
LPA: Line probe assay
LZD: Linezolid
MDR-TB: Multidrug-resistant tuberculosis
MFX: Moxifloxacin
MGIT: Mycobacterium growth indicator tube
Mtb: Mycobacterium tuberculosis
NIMDR: Nurse-Initiate and Manage Drug-resistant TB
NGS: Next-generation sequencing
Pa: Pretonamid
PCR: Polymerase chain reaction
PZA: Pyrazinamide
RCT: Randomized clinical trial
RCT: Randomized controlled trial
REDCap: Research Electronic Data Capture
RIF: Rifampicin
RR-TB: Rifampicin-resistant tuberculosis
SAE: Serious adverse event
STM: Streptomycin
TB: Tuberculosis
TZD: Terizidone
WGS: Whole-genome sequencing
WHO: World Health Organization
XDR-TB: Extensive drug-resistant.
